#### Secondary outcomes

2.7.2

The proportion of patients achieving absence of the most bothersome associated symptom (MBAS) at 2 h post-dose. Patients will self-identify their MBAS from the following symptoms at migraine onset: photophobia, phonophobia, nausea, or vomiting.The proportion of patients achieving headache relief at 2 h post-dose. Headache relief is defined as the reduction of initial pain intensity from moderate to severe levels down to mild or no intensity.The proportion of patients sustaining headache relief from 2 to 24/48 h post-dose. Sustained headache relief from 2 to 24/48 h is defined as achieving headache relief without rescue medication use and the absence of moderate-to-severe headache recurrence during 2 to 24/48 h following initial treatment.The proportion of patients sustaining headache freedom from 2 to 24/48 h post-dose. Sustained headache freedom from 2 to 24/48 h is defined as achieving headache freedom without rescue medication use, coupled with the absence of any headache recurrence (mild, moderate, or severe) during 2 to 24/48 h following initial treatment.Change in VAS scores from pre-dose to 0.5, 1, 2, 4, 24, and 48 h post-dose.Time to onset of efficacy, defined as the interval (in minutes) between drug administration and headache relief.Headache recurrence rate between 2 and 48 h post-dose. Headache recurrence is defined as patients who achieved headache relief (freedom) at 2 h post-dose, reexperiencing moderate-to-severe headache (headache of any severity) within the 2 to 48 h post-dose window.Change in TCM “Ying-Wei disharmony syndrome.” The syndrome will be assessed using the Ying-Wei Disharmony Assessment Scale (YWDAS) at baseline, 48 h post-dose, and 7 days post-dose. The scale comprises five core TCM syndromes, and the assessment framework is detailed in Table 3. Its development was grounded in clinical expertise from senior TCM practitioners and integrated classical and contemporary medical literature. Content validity was established through a rigorous review and consensus by a panel of five senior TCM experts. In a pilot study to assess feasibility and inter-rater reliability, all YWDAS assessments were independently performed by two TCM researchers who underwent standardized training using predefined scoring criteria to minimize assessment bias. The inter-rater reliability, assessed by the intraclass correlation coefficient (ICC) for absolute agreement, was 0.76 (95% CI: 0.64–0.84), indicating good agreement.

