The primary efficacy endpoint (2-h headache freedom) will be compared between groups using the chi-square test or Fisher’s exact test, with reporting of risk difference (RD) and relative risk (RR) accompanied by 95% confidence intervals (CIs). For secondary endpoints, categorical variables will be analyzed through logistic regression with baseline covariate adjustment, while continuous variables (e.g., VAS scores) will be assessed using a mixed-effects model for repeated measures (MMRM). Time to onset of efficacy will employ Kaplan–Meier curves with the Log-rank test and Cox proportional hazards models to estimate hazard ratios. To address missing data, multiple imputation will be employed under the assumption of missing at random, using fully conditional specification with predictive mean matching for continuous variables and logistic regression for categorical variables, incorporating baseline and post-baseline covariates; 20 imputed datasets will be generated, and results will be pooled using Rubin’s rules. To control for multiplicity, secondary endpoints will be grouped *a priori* into clinically coherent families, each tested using the Holm–Bonferroni method to control the family-wise error rate. The predefined families are: (1) a 2-h symptom response family comprising absence of the most bothersome symptom and headache relief at 2 h; (2) a sustained efficacy family consisting of sustained headache relief and sustained headache freedom from 2 to 24/48 h; and (3) a time-to-event and recurrence family including time to onset of efficacy and headache recurrence rate. Changes in VAS scores and the TCM syndrome score will be analyzed exploratorily and are not included in the adjustment. Safety analyses will be conducted in the safety set (SS), which includes all randomized participants receiving at least one dose of the study medication. This population will be summarized using descriptive statistics for adverse events, vital signs, and laboratory parameters, with between-group comparisons following the methods used for baseline characteristics.

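### Headache recurrence is formally tested in Holm family 3 with no stated denominator or tested version, and neither possible denominator gives a sound treatment comparison

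*Protocol article*

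**What the plan says.** Section 2.7.2 of the protocol article lists one secondary outcome, "Headache recurrence rate between 2 and 48 h post-dose", and defines it so: "Headache recurrence is defined as patients who achieved headache relief (freedom) at 2 h post-dose, reexperiencing moderate-to-severe headache (headache of any severity"). The parentheses hold a second version: relief followed by moderate or severe headache, and freedom followed by any headache. No denominator is given, and the definition does not mention rescue medication.

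Section 2.11 puts the outcome, as a single item, in "a time-to-event and recurrence family including time to onset of efficacy and headache recurrence rate". The families are "each tested using the Holm–Bonferroni method to control the family-wise error rate". Two outcomes are set apart from this scheme: "Changes in VAS scores and the TCM syndrome score will be analyzed exploratorily and are not included in the adjustment". Recurrence is not one of them. For the method, "categorical variables will be analyzed through logistic regression with baseline covariate adjustment".

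The plan already has durability outcomes that need no such restriction. Sustained relief and sustained freedom form their own family, and sustained freedom is "coupled with the absence of any headache recurrence (mild, moderate, or severe) during 2 to 24/48 h following initial treatment", with no rescue use.

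**The concern.** A patient can have a recurrence only after responding at 2 h, and response at 2 h is what the drug is meant to change. The set of people able to recur is therefore itself a result of treatment. A between-arm test of recurrence has to choose a denominator, and each choice fails in its own way:

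- **All randomised participants.** The arms remain comparable by randomisation, but more responders means more people exposed to the event. An effective drug can look worse without any loss of durability.
- **2-h responders only.** That mechanical penalty disappears, but the two groups are selected after randomisation by an outcome that treatment affects. Adjusting for baseline covariates does not restore the randomised comparison.

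At stake is an error-controlled result that cannot be read as an effect on durability. There is also a cost to a neighbouring endpoint. In a two-member Holm family the smaller p-value must pass half the family's alpha, so time to onset shares its alpha with recurrence.

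**Working it through.** **Inputs from the protocol article, section 2.9.** 2-h freedom 35% (SSF) and 11% (placebo); one-sided alpha 0.025; beta 0.1; 60 per arm calculated; 72 per arm enrolled. The documents give no recurrence rate and no 2-h relief rate, so every recurrence rate below is an assumption.

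**The plan's own figure.** Reading the 24 points as the expected difference, with unpooled variance:

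n = [0.35×0.65 + 0.11×0.89] × (1.960 + 1.282)² / 0.24² = 59.4, so 60 per arm. This matches.

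**Denominator: all randomised.** Observed rate = P(free at 2 h) × conditional recurrence r. With the same r in both arms:

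| r (assumed) | SSF, 0.35r | Placebo, 0.11r |
|---|---|---|
| 20% | 7.0% | 2.2% |
| 30% | 10.5% | 3.3% |
| 40% | 14.0% | 4.4% |
| 50% | 17.5% | 5.5% |

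The ratio is 0.35/0.11 = 3.2 for every r. SSF looks better only if its conditional recurrence is below 0.11/0.35 = 31% of placebo's. Even if SSF halves recurrence (20% vs 40%), the table would show 0.35×0.20 = 7.0% vs 0.11×0.40 = 4.4%.

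The chance of a significant two-sided Fisher result with 72 per arm and equal r, by exact enumeration (practically all of it against SSF), is:

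| r (assumed) | at 0.05 | at 0.025 (first Holm step) |
|---|---|---|
| 30% | 27% | 18% |
| 40% | 41% | 29% |
| 50% | 54% | 41% |

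The plan specifies adjusted logistic regression for categorical secondary endpoints. Fisher's test stands in for it here, and two-sided 0.05 is assumed as the family level.

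**Denominator: 2-h responders, freedom-based.** Expected numbers are 72×0.35 = 25.2 and 72×0.11 = 7.9, so about 25 vs 8.

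Suppose that everyone who responds on placebo would also respond on SSF (11%), that SSF adds 24% further responders, and that SSF has no effect on recurrence itself. The SSF rate is then a mixture of the two groups:

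- Added responders recur more (10% and 30%): (0.11×0.10 + 0.24×0.30)/0.35 = 23.7% vs 10% on placebo.
- Added responders recur less (30% and 10%): (0.11×0.30 + 0.24×0.10)/0.35 = 16.3% vs 30% on placebo.
- Equal rates: no bias.

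The sign of the bias is therefore set by assumption.

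Precision at 30% recurrence in both groups: 1.96 × √(0.21/25 + 0.21/8) = 0.365, or about 36 points. Fisher power for a true 20% vs 40% is 19% at 0.05 and 12% at 0.025.

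**Sustained freedom in all randomised participants, for comparison.** At an equal r of 30%: 0.35×0.70 = 24.5% vs 0.11×0.70 = 7.7%. Unlike the all-randomised recurrence rate, this points the right way.

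**The case against.** The best defence is that the definition speaks of patients who had already responded, which points to a responder denominator. The threefold penalty would then never arise. Its only textual support is the general statement in section 2.11 that efficacy is analysed in the ITT set, which does not mention recurrence. An article may also leave the denominator and the tested version to an analysis plan. This stands as far as it goes: the text does not fix the denominator. But settling on responders does not rescue the test, because the comparison is then selected after randomisation. The defect lies in the stated choice to test recurrence formally, not in missing detail.

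Several stronger readings are tempting, and the documents do not support them:

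- **That the comparison is both non-randomised and mechanically tilted against SSF.** The two faults belong to different denominators and do not occur together.
- **That a better drug must look worse among responders.** Swapping the assumed rates reverses the direction.
- **That the endpoint as a whole rests on about 25 vs 8 patients.** Those counts apply only to the freedom-based version. The relief-based set would be larger, by an amount the document does not give.
- **That the definition blends two events into one.** The parentheses are ordinary paired shorthand, and each version is clear. What is unstated is which one occupies the family's slot.
- **That a responder who takes rescue and stays well is counted as free of recurrence.** The definition is silent on rescue. Counting rescue as recurrence would be a preference, not a correction.
- **That the protocol calls recurrence confirmatory.** It does not use the word. It places recurrence in an error-controlled family and apart from the outcomes it calls exploratory, which amounts to formal testing.

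**Conclusion.** The point holds in this form: recurrence is formally tested in Holm family 3, its denominator and tested version are not stated, and neither denominator gives a sound treatment comparison. Over all randomised participants the distortion is a factor of 3.2 against SSF at the planning freedom rates and any equal conditional recurrence. Among responders the bias has no predictable sign, and the freedom-based comparison is very imprecise. These sizes rest on the section 2.9 response rates and on assumed recurrence rates; the two mixture results also assume that placebo responders would respond on SSF.

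The consequence is moderate. This is a secondary endpoint, the primary test is untouched, and durability is tested separately in family 2. On the all-randomised reading the error works against SSF, so it would not create a false efficacy claim.

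**What to change.** - Remove recurrence from family 3, so that time to onset no longer shares alpha with it.
- Report recurrence descriptively among 2-h responders, separately for the relief-based and freedom-based versions, with each denominator shown.
- Show rescue use between 2 and 48 h beside it.
- Base durability conclusions on sustained relief and sustained freedom in all randomised participants.

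The cost is one fewer formally tested secondary endpoint, a third family with a single member, and a documented amendment to the predefined families. Sample size and the primary analysis do not change.

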### Sample size and recruitment

2.9

The sample size was calculated based on the primary outcome measure (the proportion of patients achieving headache freedom at 2 h post-dose). Sample size determination derived from the treatment effect of 35% versus 11% placebo response (based on unpublished data), calculated through binomial proportion comparison with one-sided *α* = 0.025, *β* = 0.1, and a 24% superiority margin. This calculation yielded a requirement of 60 participants per arm. To accommodate clinical enrollment uncertainties, including anticipated attrition and protocol deviations, the adjusted enrollment target was set at 144 participants, with 72 in each group. Patient recruitment will be conducted through neurology outpatient clinics and poster-based advertising, leveraging the high patient volume across three centers to ensure sufficient enrollment.

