### Statistical analysis

2.11

All statistical analyses will be performed using SPSS 25.0 and R 4.3.1 software. Baseline characteristics will be presented through descriptive statistics [mean ± standard deviation or median (interquartile range) or frequency (percentage)]. For between-group balance testing, independent samples *t*-tests will be employed for normally distributed data with homogeneity of variance, while Mann–Whitney *U* tests are used otherwise. Categorical variables will be analyzed using chi-square tests or Fisher’s exact test based on expected frequencies. All predetermined potential confounders will be included as covariates in subsequent models for adjustment, regardless of their between-group balance status. Additionally, baseline variables showing significant imbalance will undergo sensitivity analyses to assess their confounding effects.

Efficacy analyses will be performed on both intention-to-treat (ITT) and per-protocol (PP) populations, with the ITT set including all randomized participants analyzed according to their allocated groups, regardless of protocol deviations, while the PP set will consist of participants who complied with the trial procedures without major deviations. For efficacy assessment, the use of rescue medication before the 2-h time point will be considered a treatment failure for the primary and key secondary endpoints (e.g., headache freedom, headache relief, absence of most bothersome symptom) (26). Accordingly, participants will be included in the 2-h efficacy analysis only if they have not used rescue medication before that time point, even if medication is taken afterward. Similarly, the assessment of sustained outcomes (e.g., sustained headache freedom at 24/48 h) will require no use of rescue medication within the respective 24/48-h timeframe.

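### Headache recurrence can occur only in 2-h responders, a group formed by treatment, yet it is tested between arms in a Holm family; the comparison can mislead, and the tested definition is not stated

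*Protocol article*

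**What the plan says.** The protocol article, section 2.7.2 (Secondary outcomes), gives the population at risk, with response judged at 2 h after the dose: "Headache recurrence is defined as patients who achieved headache relief (freedom". The event and window follow: "reexperiencing moderate-to-severe headache (headache of any severity) within the 2 to 48 h post-dose window". The brackets hold two endpoints in one sentence: moderate-to-severe headache after relief, and headache of any severity after freedom. No denominator is given for the rate.

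Section 2.11 (Statistical analysis) makes it part of the third multiplicity family, "a time-to-event and recurrence family including time to onset of efficacy and headache recurrence rate", with families "each tested using the Holm–Bonferroni method to control the family-wise error rate". For secondary endpoints, "categorical variables will be analyzed through logistic regression with baseline covariate adjustment". Efficacy analyses use the ITT and PP sets, with "the ITT set including all randomized participants analyzed according to their allocated groups". No responder set is defined.

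Section 2.9 gives the only response rates in the document: "treatment effect of 35% versus 11% placebo response", for headache freedom at 2 h.

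**The concern.** A participant must respond at 2 h before a recurrence can be counted. Freedom at 2 h is the primary outcome and relief at 2 h is a secondary one, so membership of the group at risk is itself an effect of treatment. A between-arm test with error control then has two possible denominators, each with a problem.

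- **All randomised participants.** A non-responder cannot have the event and is counted as having no recurrence. The arm with more responders has more participants who can relapse, so success on the primary endpoint pushes this endpoint against SSF.
- **Responders only.** The two groups are no longer those created by randomisation. Participants who respond only because of SSF have no counterpart among the placebo responders. If their relapse risk differs, the comparison is distorted, and adjustment for baseline covariates cannot be relied on to repair it.

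The Discussion calls recurrence and time to onset pivotal for clinical decisions, so readers may lean on this result. Recurrence also takes one of the two places in family 3, so the smaller p-value in that family must pass half the family level. Finally, the merged definition leaves open which of two endpoints supplies the p-value.

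**Working it through.** **Inputs from the document.** Freedom at 2 h: 35% on SSF, 11% on placebo; 60 per arm, raised to 72 (section 2.9).

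**Assumptions.** The document gives no relapse risks and no relief rates, so those below are assumed. The family level is taken as two-sided 0.05, which makes the first Holm step 0.05/2 = 0.025. Chi-square and Fisher tests stand in for the planned adjusted logistic regression, which was not evaluated.

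**1. The plan's own figure.** With unpooled variance, one-sided 0.025 and 90% power, and the 24% read as the expected difference:
n = (1.960 + 1.282)² × (0.35×0.65 + 0.11×0.89) / 0.24² = 10.507 × 0.3254 / 0.0576 = 59.4, so 60 per arm. Allowing for one-sixth loss, 60/(1 − 1/6) = 72. The stated figures are reproduced.

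**2. Who can have a freedom-based recurrence.** SSF 72 × 0.35 = 25.2; placebo 72 × 0.11 = 7.9. The chance of 5 or fewer pain-free placebo participants is P(Binomial(72, 0.11) ≤ 5) = 0.18.

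**3. All-randomised denominator.** Recurrence proportion = response rate × relapse risk among responders. With the same risk in both arms, the ratio of SSF to placebo is 0.35/0.11 = 3.18 whatever that risk is. Chance that SSF is significantly worse, 72 per arm (unadjusted chi-square):

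| Assumed risk | SSF v placebo | at 0.025 | at 0.05 |
|---|---|---|---|
| 20% | 7.0% v 2.2% | 17% | 27% |
| 30% | 10.5% v 3.3% | 28% | 41% |
| 40% | 14.0% v 4.4% | 41% | 54% |
| 50% | 17.5% v 5.5% | 52% | 64% |

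Fisher's exact test at the 30% risk gives 18% at 0.025 and 27% at 0.05. To break even, SSF would have to bring the relapse risk among its responders down to 0.11/0.35 = 31% of the placebo risk.

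**4. Responder denominator: selection.** Suppose 11% are pain-free on either treatment and a further 24% only on SSF, and SSF alters nobody's relapse risk. With assumed risks of 20% in the first group and 45% in the second, the SSF rate is (11×0.20 + 24×0.45)/35 = 37%, against 20% on placebo. With responder counts left random, Fisher's test rejects in about 6% of trials at 0.05 and 3% at 0.025. The estimate is distorted, but the rejection rate stays near nominal because the groups are small. If the two groups had equal relapse risk, there would be no distortion.

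**5. Responder denominator: power.** With Fisher's test at 0.05 and random responder counts, power is about 13% for 30% v 50% recurrence and 30% for 20% v 50%. With the counts fixed at 25 and 8, 20% v 50% gives 34%.

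**6. Relief-based version.** Relief includes freedom, so there are at least as many responders. At assumed relief of 60% v 35%, power for 30% v 50% is about 33%. On the all-randomised reading, the break-even ratio is 0.35/0.60 = 0.58 (0.55 to 0.62 over assumed relief of 55–65% v 30–40%). The direction is the same as for freedom, and the distortion is smaller.

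**The case against.** The best defence is that the definition reads most naturally with responders as the base. On that reading bias is conditional: it needs SSF-only responders to relapse at a different rate, and the document gives no relapse rates. Step 4 shows that even a sizeable assumed difference hardly raises the rejection rate. This stands. A reader might infer that either denominator necessarily gives a wrong answer, or that false claims would be frequent. The document does not support that for responders; there the faults are a possibly distorted estimate and low power.

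Second, the all-randomised figures depend on a general ITT sentence that does not say how non-responders are scored, and a condensed article may leave the denominator to a fuller document. The missing denominator alone would be no finding. But the article itself fixes a responder-only event, an error-controlled between-arm test, and analysis sets that include no responder set, and these do not fit together. The 0.05 figures apply to recurrence only if it is reached at the second Holm step; the 0.025 figures are the fairer first reading.

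Third, freedom is the harsher case, and the definition names relief first. That also stands.

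Fourth, the sustained endpoints do not replace recurrence. A reader might infer that they already answer whether SSF prevents relapse. With equal 30% relapse in both arms, sustained freedom through the recurrence window, ignoring rescue use, would be 0.35×0.70 = 24.5% v 0.11×0.70 = 7.7%, significant by chi-square in about 81% of trials at 0.05 with no effect on relapse. They are valid randomised comparisons, but they combine response with non-relapse.

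**Conclusion.** The point holds: an outcome that exists only after a treatment-dependent response should not carry a multiplicity-controlled between-arm test, and the text does not say which of the two merged definitions is tested.

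The size depends on the denominator. With all randomised participants, the penalty on SSF follows whenever SSF raises response and the relapse risk among responders is similar in both arms. At the planned freedom rates and an assumed 30% risk, it produces a significant result against SSF in about 18–28% of trials at 0.025 and 27–41% at 0.05 (Fisher to chi-square). With responders, the comparison can mislead, and power for a 30% v 50% contrast is about 13% for freedom and 33% for relief at the assumed relief rates.

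The primary endpoint and families 1 and 2 are unaffected. This should be changed, but it does not threaten the trial's main conclusion.

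**What to change.** - **Section 2.11:** remove the headache recurrence rate from family 3 and from between-group testing. Time to onset of efficacy then stands alone in that family at the full level.
- **Section 2.7.2:** report recurrence descriptively among 2-h responders, with numerator and denominator per arm, separately for the relief-based and the freedom-based definition.
- **Interpretation:** base randomised between-arm conclusions on sustained relief and sustained freedom in all ITT participants (family 2), and state that these combine response with non-relapse and do not isolate relapse.

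This takes about one sentence in each section and changes neither the sample size nor the data collected. The cost is one low-power secondary p-value, and the trial would then make no formal claim about relapse among responders.
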